16.2 AIDS-Defining Illnesses [51](#__RefHeading___Toc289425612)

List of Abbreviations

| **Abbreviation** | Definition/Term |
| --- | --- |
| AE | Adverse Event |
| AIDS | Acquired Immunodeficiency Syndrome |
| ALT | Alanine Transaminase (SGPT) |
| ALP | Alkaline Phosphatase |
| ART | Antiretroviral Therapy |
| AST | Aspartate Transaminase (SGOT) |
| CRF | Case Report Form |
| CRP | C-reactive Protein |
| DTH | Delayed type Hypersensitivity |
| EDTA | Ethylenediamine Tetra acetic Acid |
| ELISPOT | Enzyme-linked Immunosorbent Spot Assay |
| EU | European Union |
| Eur Pharm | European Pharmacopoeia |
| -GT | Gamma Glutamyl Transferase |
| GCP | Good Clinical Practice |
| GM-CSF | Granulocyte Macrophage Colony Stimulating Factor |
| GMP | Good Manufacturing Practice |
| HIV | Human Immunodeficiency Virus |
| HLA | Human Leukocyte Antigen |
| ICF | Informed Consent Form |
| ICH | International Conference on Harmonization |
| IEC | Independent Ethics Committee |
| IMP | Investigational Medicinal Product |
| IND | Investigational New Drug |
| LD | Lactate Dehydrogenase |
| MedDRA | Medical Dictionary for Regulatory Activities Terminology |
| PBL | Peripheral Blood Lymphocyte |
| PI | Principal Investigator / Sponsor |
| SAE | Serious Adverse Event |
| SOC | System Organ Class |
| Th1 | T-helper Cell Type 1 |
| Th2 | T-helper Cell Type 2 |
| ULN | Upper Limit of Normal |
| USP | United States Pharmacopoeia |
| WBC | White Blood Cells |
| WFI | Water For Injection |
| WHO | World Health Organization |
|  |  |
|  |  |

Protocol Synopsis

| Protocol Title: | | IMMUNOTHERAPY OF HIV-INFECTED PATIENTS  A single-blinded, randomized, immunogenicity, pilot study of intranasal administration of Vacc-4x with Endocine as adjuvant. | | |
| --- | --- | --- | --- | --- |
| Protocol Number: | | CT -BI-Vacc-4x/L3-2011/1 | | |
| **Name of Sponsor & Investigatio­nal Drug Substance Suppliers:** | Sponsor/Investigator: [name], Oslo University Hospital  Vacc-4x: Bionor Pharma ASA, [name]  Eurocine adjuvant: Eurocine Vaccines AB, Karolinska Institutet Science Park, [name] | | | |
| Drug Substance: | Vacc-4x: A formulation of four synthetic peptides (Vacc-10, Vacc-11, Vacc-12, and Vacc-13).  Endocine adjuvant: A lipid based nano-emulsion consisting of mono-olein and oleic acid in 0.15 M NaOH at pH 8.0. | | | |
| Investigational Drug Product: | Vacc-4x with Endocine adjuvant | | | |
| Phase of Development: | Pilot phase I/II | | Indication: | Human immunodeficiency virus-1 (HIV-1) infection |
| **Study Center(s):** |  | | | |
| Objectives: | **Primary:**  The primary objective of this study is to evaluate the safety of intranasal administration of Vacc-4x with Endocine as adjuvant at three different dose levels.  **Secondary:**   - To evaluate cellular immune response to Vacc-4x in vitro. - To evaluate cellular immune response to Vacc-4x in vivo by DTH. - To evaluate the effect on CD4 counts and viral load (HIV-1 RNA).   **Exploratory:**   - To evaluate the humoral immune responses in mucosal fluids (nose, rectum, vagina (optional)) and in serum. - To evaluate time dependent change in Vacc-4x specific T cell responses. - To evaluate the immune response in urine. | | | |
| Study Design: | A single-blinded, randomized, sequential study. | | | |
| Planned Number of Subjects: | Four groups of patients with 6 patients in each group. Total 24 patients | | | |
| Subject Population: | HIV-infected patients | | | |
| Diagnosis and Main Criteria for Inclusion/ Enrollment: | **Inclusion criteria:**   - Age above 18 years, both genders. - HIV positive at least one year. - Clinically stable on ART for the last 6 months (changes in therapy is allowed as long as the viral load is stable). - Documented viral load (HIV-1 RNA) less than 50 copies/mL for the last six months. - Documented stable CD4 cell count ≥ 400x106/L. - Nadir (lowest ever) CD4 cell count ≥ 200x106/L. - Signed informed consent.   **Exclusion criteria:**   - Reported pre-study AIDS-defining illness within the previous year. - Malignant disease. - On chronic treatment with immunosuppressive therapy. - Unacceptable values of the hematologic and clinical chemistry parameters, as judged by the Principle Investigator (or designee), including creatinine values >1.5x upper limit of normal (ULN), and AST (SGOT), ALT (SGPT) and alkaline phosphatase values >2.5x ULN. - Concurrent chronic active infection such as chronic viral hepatitis B or C or active tuberculosis. - Pregnant or breastfeeding women. - Women of childbearing potential not using reliable and adequate contraceptive methods (defined as: use of oral, implanted, injectable, mechanical or barrier products for the prevention of pregnancy; practicing abstinence; sterile) during the study, or sexually active male patients with partners of childbearing potential unwilling to practice effective contraception during the study. - Current participation in other clinical therapeutic studies. - Incapability of compliance to the treatment protocol, in the opinion of the Investigator. | | | |
| Reference Product: | None | | | |
| Treatment Regimen: | During the Treatment Period, all subjects will remain on their ART and receive four immunizations at weeks 1, 2, 3 and 4 with either :  ***A low dose group***: 80 µg Vacc-4x (20 µg pr. peptide) divided into two administrations;  40 µg Vacc-4x in 150 µl Endocine for each nostril.  ***A medium dose group***: 400 µg Vacc-4x (100 µg pr. peptide) divided into two administrations;  200 µg Vacc-4x in 150 µl Endocine for each nostril.  ***A high dose group***: 1200 µg Vacc-4x (300 µg pr. peptide) divided into two administrations;  600 µg Vacc-4x in 150 µl Endocine for each nostril.  ***A zero dose group***: Only adjuvant divided into two administrations;  150 µl Endocine for each nostril. | | | |
| Duration of Participation: | Screening: 1-4 weeks.  Study period: 8 weeks (4 weeks immunization period + 4 weeks follow-up) | | | |
| Endpoints: | **Safety endpoints:**   - AEs recorded at each scheduled and unscheduled visit - Clinical laboratory evaluations (clinical chemistry, hematology) at screening, week 1,   week 4 and week 8 (Termination).   - Viral load (HIV-1 RNA) at screening, week 1, week 4 and week 8 (Termination). - Physical examinations at screening, week 1, week 4 and week 8 (Termination). - Vital signs (heart rate, blood pressure) at screening, week 1, week 4 and week 8   (Termination).  **Efficacy endpoints:**   - Immune response – T cell immunogenicity: - T cell responses to Vacc-4x at screening and week 1 compared to week 8CD4 counts at screening, week 1, and week 8 (Termination). - DTH (both induration and erythema) at week 8 in terms of observed areas (mm2) and also in terms of a positive test, defined as an area ≥10 mm2.   **Exploratory endpoints:**   - Humoral immune responses to Vacc-4x in mucosal fluids and in serum. - Time dependent change in Vacc-4x specific T cell responses. - Immune response in urine.   Post-study follow-up (T cell responses in blood and/or mucosal secretions): At 6 months interval Week 28 (pending documented immunogenicity week 8 in Vacc-4x group), Week 52 (pending documented immunogenicity Week 28) and final Week 76 (pending documented immunogenicity Week 52). | | | |

# introduction

## Background information

Human immunodeficiency virus (HIV) infects the CD4 subset of T-cells that are critical for initiating immune responses to infection. The level of CD4 cells in the blood is a marker of a patient’s immunological status. Before the advent of HIV medication, it was clear that sustained immune responses to the HIV capsid protein, p24, were inversely correlated with disease progression (CD4 cell decline) ([Forster, 1987](#Forster1987); [Weber, 1987](#Weber1987)). When CD4 counts are below 200x106/L, immune status is reduced to a level that allows for opportunistic infections. In contrast, long term non-progressor patients showed sustained immune responses to HIV p24. Sustained immune responses to p24 appear to be essential to maintain CD4 counts and thereby restrict disease progression.

Vacc-4x is a peptide-based HIV immunotherapy. The primary objective of Vacc-4x immunotherapy is to strengthen the immune system’s response to HIV p24. The immune response to HIV-1 following immunization with Vacc-4x could overcome the hazards (opportunistic infection, death) associated with subjects on antiretroviral therapy (ART) with insufficient regain of CD4 counts.

ART dramatically reduces the level of virus in circulation in the body, thereby allowing the immune system to focus on the therapeutic vaccine that is administered. ART also allows for the generation of new naïve CD4 cells that can be triggered by the immunotherapy to generate new immune responses to HIV-1. However, recently published results indicate that residual HIV-1 replication may be ongoing despite modern ART ([Dinoso, 2009](#Dinoso2009); [Trono, 2010).](#Trono2010) This may increase the patient’s susceptibility to immune activation and poor immune reconstitution, which both may lead to complicating disease. Adding Vacc-4x immunizations to ART would potentially provide further improved control of virus replication.

Vacc-4x is comprised of peptides that are modified from conserved domains of HIV p24, the major capsid protein of HIV. So far it has been administered intradermally following the administration of granulocyte macrophage colony stimulating factor (GM-CSF), which is used as a local adjuvant. GM‑CSF was chosen because of its ability to facilitate dendritic cell maturation and migration to the lymph nodes for antigen presentation ([Disis, 1996](#Disis1996); [Banchereau, 1998](#Banchereau1998)).Dendritic cells are targeted because they are the most potent antigen presenting cells of the immune system and have the capacity to carry out ‘cross presentation’ during which foreign antigens are presented on both human leukocyte antigen (HLA) classes 1 and 2 (Figure 1).

Figure 1 Simplified Diagram Showing the Two Pathways for Peptide Digestion Leading to Presentation at the Cell Surface

[figure not shown]

Dendritic cells ingest peptides into small vesicles. If they follow the HLA class II pathway, they are cleaved within the vesicle that subsequently fuses with one carrying the HLA class II molecule. Some of the peptide fragments bind to the HLA class II and reach the cell surface attached to this molecule. The peptide fragment is recognized by a CD4 cell that docks onto the HLA molecule. Dendritic cells have the unique ability to transfer peptides to the HLA class I pathway. Here, the peptides are digested by the proteasome. The peptide fragments are then transported into specialized compartments of the cell where the HLA class I molecules reside. The peptides attach themselves to the HLA class I molecule and are transported to the cell surface. Peptide fragments are recognized by a CD8 cell that docks onto the HLA class I molecule. (From: [Sommerfelt, 2004)](#Sommerfelt2004)

A consequence of dendritic cell stimulation by peptides is the proliferation of both CD4 and CD8 cells. The CD8 cells acquire the ability to recognize infected cells expressing HIV epitopes that are represented in the modified peptides. The Vacc-4x immunotherapy therefore aims to stimulate cell-mediated immunity. Since HIV can persist in quiescent T cells and memory cells ART cannot cure the disease, but must be a life-long treatment. Stimulation of the cell-mediated immunity might help reaching the HIV reservoirs that lie in sites poorly accessed by current ART (such as gut and brain).

## Investigational product

Vacc-4x

Vacc-4x is comprised of peptides that are modified from conserved domains of HIV p24, the major capsid protein of HIV. Prior to the introduction of ART, it became clear that the survival time during HIV-1 infection was related to immune responsiveness to the major capsid protein p24. Sustained immune responses to p24 should maintain CD4 counts and delay disease progression. It has been shown that p24 antigens (not virus-associated) can persist during ART. Increasing levels of p24 antigen while on ART are inversely correlated with CD4 count and disease progression. The Vacc-4x peptides are based on conserved domains of the major capsid protein p24.

## Nonclinical studies

Conclusions from Nonclinical Studies

The results of non-clinical single-dose studies in mice and rats indicate that the dose levels of intravenous Vacc-4x elicited no adverse reactions and that the no effect level was in excess of 3 mg/kg, which constitutes a 500‑fold safety margin over the planned human dose level.

In a rabbit study the effect of Vacc-4x was evaluated in the presence of concomitant GM-CSF, the adjuvant used in the clinical program. Local intradermal reactions such as erythema and edema were noted, however, similar effects were noted in control animals both macroscopically and histologically. These local reactions were slightly more pronounced in the Vacc-4x treated animals. There were no systemic reactions in this study. These data indicate that Vacc-4x has no limiting toxicology in a model that is relevant to the proposed clinical study.

## Clinical Studies

Four clinical studies have been conducted with Vacc-4x; a Phase I clinical study at the University of Bergen, Norway including 11 patients, and a Phase II clinical study at Ullevål University hospital in Oslo, Norway that enrolled 40 chronic HIV‑infected patients ([Åsjö, 2002;](#Åsjö2002) [Kran, 2004](#Kran2004)). In a follow-up of the patients at former Ullevål university hospital 7 years after immunization, most patients who earlier had responded to Vacc-4x now showed detectable CD4 memory cells which could be activated (Report CTN-BI/Vacc-4x/2009/1 2011-02-02). In addition, one phase II study has just been finished, i.e. a randomized, double-blind, multicenter, immunogenicity study of Vacc-4x versus placebo in patients infected with HIV-1 who have maintained an adequate response to ART (EudraCT Number 2007-006302-13). This study included 135 patients. In this study no effects on CD4 counts was seen but there was a favorable effect on viral load.

## Adjuvant

The Endocine adjuvant is a lipid based nano-emulsion consisting of mono-olein and oleic acid in 0,15 M NaOH at pH 8,0. The nanoparticles have a size of less than 100 nm. The appearance of the nanoparticles is a white opalescent liquid with reological characteristics similar to water.

The two lipids are endogenous and upon administration to a mammal they are incorporated into the normal biochemical pathways within the body and metabolised.

Both of the lipids are approved for pharmaceutical use (Ph Eur. 6th Ed. (6:3) 2009).

***Toxicology studies of Endocine:***

Safety testing of Endocine as adjuvant for an influenza vaccine has been performed at Visionar AB in Uppsala, Sweden in order to assess general toxicity of the vaccine formulations. In one study ([Visionar Final Report of Study VP-07-07 (2007](#VisionarReport2007))), it was concluded that the H1N1 antigen used in this study provoked an immunological response which stimulated antibody production against H1N1 virus. The severity and frequency of lesions in adjuvant or adjuvant + virus antigen treated animals were similar to frequency of lesions found in vehicle treated animals. This indicates that the adjuvant or adjuvant + virus antigen did not produce mucosal lesions.

Health records haematology, clinical chemistry and histopathology analyses indicate that the vaccine, after repeated administration, did not cause general toxic reactions in rats.

In a second toxicology study in rats general toxicity of the vaccine formulation was assess ([Visionar Final Report of Study VP-08-35-01 (2009))](#VisionarReport2009). The data assembled show that nasal administration of the adjuvant anionic adjuvant alone or in combination with the A/Solomon Islands/3/06-like IVR-145 (H1N1) whole cell influenza virus antigen produced very few histopathological effects. These can be explained by a normal reaction against immunologically active agents or caused at blood sampling, however. Taking all data collected in this study into consideration it seems as the anionic adjuvant (at concentrations of 0.5 or 2%) alone, or in combination with the A/Solomon Islands/3/06-like IVR-145 (H1N1) whole cell influenza virus antigen, was tolerated by rats.

## Rationale for the Study

Adding Vacc-4x immunizations to ART could potentially reduce virus replication further by removing infected cells and thereby act to slow down the disease progression. Thus, by administering Vacc-4x to subjects who are clinically stable on ART, immune responses against HIV p24 should be boosted leading to improved health status.

In the previous studies with Vacc-4x it has been used as an intra-dermal administration using GM-CSF as an adjuvant. Since intra-dermal administration is dependent on trained health personal it is of interest to test a more simple administration route.

This study is to evaluate safety and immune response (T-cell response) after mucosal delivery (intranasal administration) of three different doses of Vacc-4x using Endocine as adjuvant to patients stable on ART.

### Dose

Vacc-4x

Based on previous studies, 400 µg Vacc-4x (100 µg pr. peptide) and 1.2mg Vacc-4x (300 µg pr peptide) were chosen as the medium and highest dose group. In addition a low dose group of 80 µg Vacc-4x (20 µg pr. peptide) is to be included.

A DTH test (Vacc-4x 400 µg intra-dermal) will be done at week 8.

### Immunization schedule

The same 4 week initiation dosing regimen (weeks 1, 2, 3 and 4) as used in previous studies will be used.

### Use of adjuvant Endocine

Peptide vaccines are poorly immunogenic by themselves. To induce measurable levels of T‑helper cell type 1 (Th1) or type 2 (Th2) immune responses against these peptides, adjuvant is often required.

The Vacc-4x nasal vaccine is prepared by a mixing of the Endocine adjuvant nanoparticles and the Vacc-4 peptides.

## Potential Risks and Benefits

Participants will provide important scientific information that may contribute to improved management of future HIV-positive subjects. Potential benefits for participants include a possible sustained improvement in the immune response to p24 and HIV. All patients will continue their regular ART regimen throughout the study and the study design does not involve scheduled ART interruption. Potential risks include the discomfort and inconvenience associated with the immunizations and the risk of known or unknown side effects of exposure to Vacc-4x given as intranasal administration with Endocine as adjuvant.

After intranasal administration the most common types of adverse events are expected to be related to local irritation of the nasal mucosa.

# Study objectives AND ENDPOINTS

## Study objectives

### Primary objective

The primary objective of this study is to evaluate the safety of intranasal administration of Vacc-4x with Endocine as adjuvant at three different dose levels.

### Secondary objectives

- To evaluate cellular immune responses to Vacc-4x in vitro.
- To evaluate cellular immune responses to Vacc-4x in vivo by DTH in comparison to DTH from unvaccinated patients on effective ART (data from preceding study).
- To evaluate the effect on CD4 counts and viral load (HIV-1 RNA).

### Exploratory objectives

- To evaluate the immune response in mucosal fluids (nose, rectum, vagina (optional)) and in serum.
- To evaluate time dependent change in Vacc-4x specific T cell responses.
- To evaluate the immune response in urine.

## Study endpoints

### Safety endpoints

- AEs recorded at each scheduled and unscheduled visit
- Clinical laboratory evaluations (clinical chemistry, hematology) at screening, week 1, week 4 and week 8 (Termination).
- Viral load (HIV-1 RNA) at screening, week 1, week 4 and week 8 (Termination).
- Physical examinations at screening, week 1, week 4 and week 8 (Termination).
- Vital signs (heart rate, blood pressure) at screening, week 1, week 4, and week 8 (Termination).

### Efficacy endpoints

- Immune response – T cell immunogenicity:

T-cell responses to Vacc-4x at screening and week 1 compared to week 8.

- CD4 counts at screening, week 1, week 4 and week 8 (Termination).
- DTH (both induration and erythema) at week 8 in terms of observed areas (mm2) and also in terms of a positive test, defined as an area ≥10 mm2.

### Exploratory endpoints

- Humoral immune response to Vacc-4x in mucosal fluids and in serum.
- Time dependent change in Vacc-4x specific T cell responses.
- Immune response in urine.
- Post-study follow-up (T cell responses in blood and/or mucosal secretions): At 6 months interval Week 28 (pending documented immunogenicity week 8), Week 52 (pending documented immunogenicity Week 28) and final Week 76 (pending documented immunogenicity Week 52).

# study design

## Overall study design and flow chart

The study is a single-blinded, sequential design, single centre pilot study in HIV-positive subjects on treatment (ART). Twenty-four subjects will be enrolled into one of four treatment groups.

| **Group** | **Treatment** | **No. of subjects in Europe** |
| --- | --- | --- |
| 1 | 80 µg Vacc-4x + Endocine* | 6 |
| 2 | 400 µg Vacc-4x + Endocine* | 6 |
| 3 | 1.2 mg Vacc-4x + Endocine* | 6 |
| 4 | Endocine* | 6 |

* adjuvant

Subjects who have been HIV-positive and stable on ART for the last 6 months and CD4 cell counts ≥400x 10 6 /L and who meet the other inclusion and exclusion criteria will be eligible for the study. The duration of the main study is 8 weeks plus a screening period of up to 4 weeks. A study flow chart is presented in Table 2.

Table 2 Study Flow Chart

| **PARAMETERS** | **Weeks**  **Day** | **-4** | **1 2 3 4**  **1 8 15 22** | | | | | **8 END**  **50-53 (DTH)** | | |
| --- | --- | --- | --- | --- | --- | --- | --- | --- | --- | --- |
| Visits | 1 | 2 3 4 5 | | | | |  | | |
|  | Scree-ning | Immunization  period | | | | | | Follow-up  period | |
| Randomization | | x |  |  |  |  |  |  | |  |
| Immunizationa)  VACC-4x / Endocine | |  | x | x | x | x |  |  | |  |
| DTH-test b) | |  |  |  |  |  |  |  | | x |
| Adverse event | |  | x | x | x | x |  |  | | x |
| Vital signs/Physical examinationc) | | x | x |  |  | x |  |  | | x |
| Blood sample:  general safety d) | | x | x |  |  | x |  |  | | x |
| Blood sample:  Viral load (HIV-1 RNA), CD4 | | x | x |  |  | x |  |  | | x |
| Blood sample:  T-cell responsee) | | X | X | x | x | X |  |  | | X |
| Sampling of mucosal secretions | |  | x |  |  | x |  |  | | x |
| Urine sample | |  | x |  |  |  |  |  | | x |
| Inclusion/Exclusion | | x |  |  |  |  |  |  | |  |
| Informed consent | | x |  |  |  |  |  |  | |  |

1. 150µl to be administered in each nostril
2. DTH skin reaction; to be registered at 48 hours after immunization.
3. Body weight, height (at baseline only), blood pressure, heart rate, concomitant disease, concomitant medication
4. Hb, CRP, WBC (incl. diff), Platelets, Creatinine, Na, K, AST, ALT, LDH, ALP, -GT, Albumin, Total Bilirubin, Beta2-microglobulin. In addition, the subjects HLA type can be registered.
5. For cryopreservation of PBMC to T cell response assays with optional samples for T cell response kinetics and optional assays on fresh blood samples. X, mandatory assay time points; x, optional time points pending on responsiveness.

During the Treatment Period, all subjects will remain on their ART and receive four immunizations at Weeks 1, 2, 3 and 4, with Vacc‑4x including Endocine as adjuvant.

The study is sequential, meaning that the first five subjects receive either adjuvant only (two patients) or the lowest dose (three patients) 80 µg Vacc-4x together with Endocine (given as 40 µg Vacc-4x as 150µl Endocine solution in each nostril). If the safety evaluation after two weeks is ok, the next dose level will be started, see Figure below:

[figure not shown]

##

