#### Visit 2 (Week 1 - Day 1)

This visit will occur at least five days but not more than 28 days after the screening visit. The following procedures will be performed in the following order (it is important that all blood samples are taken before drug administration):

- Review of concomitant medications and AEs
- Physical examination, including weight
- Vital signs
- Clinical chemistry and hematology and optional HLA type
- Viral load (HIV-1 RNA) and CD4 counts
- T-cell responses
- Collection of mucosal sections
- Collection of urine
- Administration of study drugs via intranasal administration

The subject should remain in the clinic for 30 min after the administration of study drug to be monitored for adverse reactions to the immunization.

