#### Visit 3 (Week 2 – Day 8(1))

The following procedures will be performed in the following order:

- Review of concomitant medications and AEs
- Administration of study drugs via intranasal administration
- T-cell responses (optional)

The subject should remain in the clinic for 30 min after the administration of study drug to be monitored for adverse reactions to the immunization.

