### Physical examination

Physical examination will be performed at screening, week 1, week 4 and week 8 (end of study). Physical examination will include height (only at screening or week 1) and weight and evaluation of the subject’s medical condition. Any new or worsening of medical condition compared to the pretreatment condition (pre-dose on Day 1) should be recorded as an AE on the CRF.

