### Vital signs

At screening, week 1, week 4 and week 8 (end of study) vital signs (heart rate, systolic and diastolic blood pressure) will be measured prior to administration of study drug (if applicable) with the subject in the sitting position. Vital signs will be measured after the subject has been sitting at rest for 5 minutes.

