### HIV viral load (HIV-1 RNA)

A blood sample (approximately 10mL) will be collected in tubes containing EDTA at screening and week 1, week 4 and week 8 (end of study). Tests will be performed at the local hospital laboratory.

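### Counted from first dose, the two-week safety review in Section 4.1 opens the next dose level 7 days before the first scheduled post-dose laboratory, HIV-1 RNA, vital-sign and examination data

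*Protocol*

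**What the plan says.** Section 4.1 describes a sequential study. The first five subjects receive adjuvant only (two) or 80 µg Vacc-4x with Endocine (three). Escalation then depends on one condition: "If the safety evaluation after two weeks is ok, the next dose level will be started". The sentence points to a figure that our copy does not show. The visible text gives neither a starting point for the two weeks nor the data to be reviewed.

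Section 3.2.1 names five safety endpoints: adverse events, laboratory tests, viral load, physical examination and vital signs. Adverse events are recorded at every visit, scheduled or not. The other four follow a sparser schedule, for example "Clinical laboratory evaluations (clinical chemistry, hematology) at screening, week 1, week 4 and week 8 (Termination"). Sections 8.3.2 to 8.3.5 and the flow chart give the same time points.

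Section 7.3.2 sets the order of procedures within visits. At Visit 2 (Day 1), "it is important that all blood samples are taken before drug administration", and the examination is listed ahead of dosing. Section 8.3.3 says that vital signs "will be measured prior to administration of study drug (if applicable". The safety content of Visit 3 (Day 8) is "Review of concomitant medications and AEs", followed by 30 minutes of observation in the clinic after dosing. Visit 4 (Day 15) is the same. Visit 5 (Day 22) repeats the full panel before the fourth dose.

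**The concern.** Safety is the primary objective in Section 3.1.1: "The primary objective of this study is to evaluate the safety of intranasal administration of" Vacc-4x with Endocine at three dose levels. The two-week review is the only escalation rule in the visible text. Sections 2.1 and 2.6 say that earlier Vacc-4x use was intradermal with GM-CSF, so that experience does not directly cover this route and adjuvant.

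If the review takes place two weeks after first dose, the next level could open without a post-dose liver, renal, haematology, CRP or HIV-1 RNA value from subjects who have not reached Day 22. Adverse-event review does not replace those values. Section 9.1.3 keeps clinically significant laboratory abnormalities off the adverse-event page unless signs or symptoms are present, and no safety blood sample is scheduled between the pre-dose Day 1 sample and Day 22. A symptom-free rise in ALT or creatinine would not be seen at the gate.

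**Working it through.** No power or sample-size formula applies, because Section 11.1 sets the group size for descriptive purposes. The check is calendar arithmetic.

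**Inputs**
- Doses on Days 1, 8, 15 and 22 (Section 4.1, flow chart).
- Panel of laboratory tests, HIV-1 RNA, vital signs and examination at screening, Day 1, Day 22 and Week 8 (Sections 3.2.1 and 8.3.2 to 8.3.5). The Day 1 and Day 22 sets come before that day's dose (Sections 7.3.2 and 8.3.3). The first post-dose panel is therefore Day 22.
- Review two weeks (14 days) after an unstated starting point (Section 4.1).

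**Gap for one subject.** Review day = starting day + 14. Gap = 22 − review day.

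| Two weeks counted from | Review day | Gap to first post-dose panel |
|---|---|---|
| First dose (Day 1) | 1 + 14 = 15 | 22 − 15 = 7 days short |
| Second dose (Day 8) | 8 + 14 = 22 | 22 − 22 = 0 |
| Third dose (Day 15) | 15 + 14 = 29 | panel 7 days earlier |
| Fourth dose (Day 22) | 22 + 14 = 36 | panel 14 days earlier |

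The shortfall arises only when counting from first dose. In the second row the samples are drawn on the review day itself, so results may still be pending. If the bracketed 1 after the Visit 5 day is a window of ±1 day (an assumption, as the sign is lost in our copy), the first-row gap runs from 21 − 15 = 6 to 23 − 15 = 8 days.

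**Data in hand on the first-dose reading.** On Day 15, 1 of 5 safety endpoints (adverse events) has scheduled post-dose data. On Day 22 it is 5 of 5. A Day 15 review covers doses 1 and 2, since the third is due that day. The Day 22 panel covers doses 1 to 3.

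**Several subjects in a step.** Let subject i start on study day s_i and the last subject on s_L. Counting from the last subject's first dose, the review is on s_L + 14, and subject i's panel is on s_i + 21. The panel has been taken by the review only if s_i + 21 ≤ s_L + 14, that is, s_i ≤ s_L − 7. Subjects who started at least a week before the last one qualify. The last subject never does.

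**Dose steps opened by the gate.** 400/80 = 5-fold, and 1200/400 = 3-fold.

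**The case against.** The strongest objection is that the escalation scheme is referred to a figure we cannot see. That figure may start the two weeks at a later dose or show a later review. The first-dose count is the plainest reading of the visible sentence, but the sentence does not settle it. This limit stands, and the point is conditional on it.

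Two stronger readings are tempting, and the documents support neither.
- **That the protocol contradicts itself.** Section 4.1 never says that the review must cover all five endpoints of Section 3.2.1. A gate based on adverse events and tolerability is consistent with every section cited.
- **That the gate has no safety data.** Adverse events are reviewed on Days 8 and 15, and each dose is followed by 30 minutes of observation. Section 9.1.5 allows extra laboratory tests to investigate an event. Section 2.7 expects mainly nasal irritation, which this review should detect. Section 5.4.1 holds further dosing of a subject with a severe local reaction, or a related Grade 3 or 4 systemic one, until the suppliers are consulted. Section 12.3 allows the study to be stopped. These provisions act on individual subjects or give general discretion. None supplies the missing panel at the gate.

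It is also fair that only the peptide dose escalates. Every arm receives the same 150 µl per nostril (Section 6.1.2). Section 2.3 cites a 500-fold margin from intravenous animal work, Section 2.5 describes nasal rat toxicology of Endocine, and Section 2.6.1 bases the two upper doses on earlier studies. This reduces the urgency but does not replace post-dose laboratory values for the combination under test.

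**Conclusion.** The point holds in conditional form. If the two weeks run from first dose, the review precedes the first scheduled post-dose laboratory, HIV-1 RNA, vital-sign and examination data by 7 days (6 to 8 with the assumed visit window). It then rests on adverse-event and concomitant-medication review plus the 30-minute observations for every subject not yet at Day 22. The gate is incomplete rather than empty. The conclusion rests on the first-dose reading and on the schedule, which is the same throughout the protocol. If the figure already sets Day 22 or later with results in hand, only a clarification of the wording in Section 4.1 remains. The change is worth making because the panel that would complete the gate is already planned.

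**What to change.** State in Section 4.1 that the next dose level opens only after all subjects in the current step have completed the Day 22 visit and its already planned safety results have been reviewed. Keep any later time point that the figure sets, so that nothing is brought forward.

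The change needs amendment text only. The total stays at 24 subjects, and no visit or sample is added. The cost in time depends on where the present gate starts:
- **Last subject's first dose:** (s_L + 21) − (s_L + 14) = 7 days per step, plus local laboratory turnaround. With two gates (80 to 400 µg and 400 to 1200 µg, assumed), that is 2 × 7 = 14 days in all, plus turnaround.
- **First subject's first dose (s_1):** (s_L + 21) − (s_1 + 14) = 7 + (s_L − s_1) days per step, plus turnaround. This is longer by the time taken to enter the step.
- **Figure already sets Day 22 or later with results in hand:** no delay.
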